### Safety measurements

2.8

All adverse events must be documented in detail in the Case Report Form (CRF), including symptom characteristics, severity, onset/duration, management measures, and outcomes. An objective assessment of the causality between the event and the acupuncture intervention is required. The attending physician may discontinue a participant’s involvement based on clinical judgment; such decisions require the signature and date from the researcher.

Regarding MRI examinations, participants may experience discomfort from the prolonged scanning time and acoustic noise. Headphones will be provided to reduce noise exposure. If a participant remains unable to tolerate the procedure, the scan may be terminated by mutual agreement, and this will be recorded as a study withdrawal. The decision to resume scanning after a rest period will be based on the physician’s assessment of the participant’s readiness.

## Results

3

### Immediate brain responses during task fMRI

3.1

#### Common brain effects

3.1.1

Both verum and sham acupuncture may commonly activate a brain network involving the anterior cingulate cortex, anterior insula, primary/secondary somatosensory cortices, and prefrontal cortex. This network is responsible for processing stimulus salience, bodily sensations, and cognitive appraisal, reflecting the non-specific effects of acupuncture. That is, this brain activity largely stems from shared components such as attention, sensation, and expectation elicited by the skin penetration itself, overlapping with the neural substrates of placebo effects.

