### Study design

2.1

This prospective, single-center, randomized, single-blind, placebo-controlled study will enroll 250 healthy participants. Participants will undergo acupuncture in separate sessions at one of seven predefined acupoints (verum acupuncture) and its corresponding non-acupoint (sham acupuncture), with a 1-week interval between sessions (18) (Figure 1). All participants will undergo two identical fMRI scanning sessions, separated by a 1-week interval, which corresponds to the washout period between the two acupuncture interventions. Each session will include resting-state fMRI scans before and after acupuncture, as well as task-based fMRI scans during acupuncture (Figure 2). The sequence of verum and sham protocols will be randomized across all fMRI runs, and the order of presentation will be counterbalanced across subjects (18).

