### Sample size

2.3

Currently, there are no standardized criteria for determining sample sizes in MRI studies, as they are often constrained by practical considerations such as scanning time and cost. Based on an efficiency analysis of sample size estimation in MRI research, a previous study indicated that approximately 12 participants are required to achieve 80% power at the single-voxel level for typical activation effects (19). In line with this reference and considering the study design, we set a sample size of 30 participants per acupuncture point. Each volunteer will undergo both verum and sham acupuncture at the same acupoint, resulting in a total of 210 experimental sessions. To account for potential data loss due to head motion or participant dropout, we plan to enroll a total of 250 subjects.

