#### Sham acupuncture group

2.5.2

Non-acupoints are localized at 1.5 cm lateral to the corresponding verum acupoints (Table 1), outside meridian trajectories and neurovascular bundles, avoiding tender points and hair follicles (Figure 3). Identical opaque, non-metallic sponge pads, as used in the verum group, will be placed on the skin surrounding the target area after disinfection. Blunt-tipped placebo needles (Suzhou Acupuncture & Moxibustion Appliance Co., Ltd., China; 0.25 × 30 mm) will be vertically placed on the skin surface without penetration, maintaining slight tactile pressure. Hence, the Deqi experience of the participants will not be overemphasized. Except locations of acupoints and needle penetration, the manipulation procedures and course will be the same with the verum acupuncture group (Figure 4).

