#### MRI scanning protocol

2.6.2

The fMRI data will be acquired with the Siemens Prisma 3.0T MRI (Siemens, Munich, Germany) at the Shenzhen Traditional Chinese Medicine Hospital, Shenzhen, China. High-resolution T1-weighted structural images will be acquired using a magnetization-prepared rapid gradient-echo (MPRAGE) sequence with the following parameters: repetition time (TR) = 2,200 ms, echo time (TE) = 2.45 ms, field of view (FOV) = 256 mm × 256 mm, isotropic voxel resolution = 1 × 1 × 1 mm^3^, 175 slices with no interslice gap, and a flip angle (FA) of 8°. For resting-state and task-based functional scans, the parameters will be as follows: TR = 2,000 ms, TE = 30 ms, 37 slices, in-plane resolution = 64 × 64, voxel resolution = 3.75 × 3.75 × 4 mm^3^, and 240 volumes acquired per run. Before the scanning session, participants will be positioned supine with their heads immobilized using a pillow. They will be instructed to keep their eyes closed, remain relaxed, avoid deliberate mental activity, and breathe naturally. Foam earplugs are provided to minimize scanner noise. Scanning commences after participants have acclimated to the environment.

Both verum and sham acupuncture protocols will follow the procedure below (Figure 2). After 20 min of quiet rest, the subject will first undergo a 14-s locator scan to determine the imaging range. This will be followed by a 4-min and 39-s 3D high-resolution T1-weighted imaging sequence to acquire anatomical structural information. A pre-acupuncture resting-state fMRI scan lasting 6 min and 6 s will then be performed. Subsequently, a licensed acupuncturist will enter the MRI scanning room to administer acupuncture on the right limb using a block paradigm: three 60-s cycles of twisting needle manipulation will alternate with three 60-s cycles of needle-retaining baseline states. Concurrently, task-based fMRI scanning will be conducted for 6 min and 6 s. Following needle removal, a 6-min and 6-s post-acupuncture resting-state fMRI scan will be acquired.

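### Section 3.1.1 attributes activation shared by verum and sham to skin penetration, but the sham in 2.5.2 does not penetrate, so any penetration response falls in the verum–sham difference that 3.5 reads as specific

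*Protocol article*

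**What the plan says.** Section 3.1.1 (Common brain effects) anticipates that "Both verum and sham acupuncture may commonly activate a brain network". It treats this shared activity as non-specific and explains most of it by "attention, sensation, and expectation elicited by the skin penetration itself, overlapping with the neural substrates of placebo effects".

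Section 2.5.2 (Sham acupuncture group) describes the control. "Non-acupoints are localized at 1.5 cm lateral to the corresponding verum acupoints", and the blunt needles "will be vertically placed on the skin surface without penetration, maintaining slight tactile pressure". It then lists how sham departs from verum: "Except locations of acupoints and needle penetration, the manipulation procedures and course will be the same with the verum acupuncture group". Under 2.5.1 the verum needle is inserted 2 cm.

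Section 2.6.2 (MRI scanning protocol) sets the task for both conditions: "three 60-s cycles of twisting needle manipulation will alternate with three 60-s cycles of needle-retaining baseline states".

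Section 3.5 (Blinding assessment and placebo effects) equates common effects with placebo and differential effects with specific effects, and holds that the design can separate the two.

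On location, section 2.1 gives each participant "one of seven predefined acupoints (verum acupuncture) and its corresponding non-acupoint (sham acupuncture"), while section 2.3 says: "Each volunteer will undergo both verum and sham acupuncture at the same acupoint".

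**The concern.** Sections 3.1.1 and 2.5.2 put penetration on opposite sides of the common/differential split. In 3.1.1 it is a shared, placebo-like component. In 2.5.2 it is a designed difference, present under verum and absent under sham. Since 3.5 builds its separation of placebo from specific effects on that split, the side on which penetration falls decides how the results may be read.

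Two misreadings follow if 3.1.1 stands beside 2.5.2. Activation shared with a non-penetrating control could be described as a response to penetration, on which that control gives no evidence. And a penetration response, which 3.1.1 itself classes as non-specific, would sit inside the difference that 3.5 calls specific. The Introduction's first objective is to isolate the effect of a defined acupoint from non-specific responses, so the second misreading bears on the trial's main claim.

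**Working it through.** No arithmetic applies: the point depends on no sample size, power or threshold, and the plan states no figure to reproduce. The check sets the sections side by side.

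**Step 1: what differs between the conditions, by 2.5.1 and 2.5.2.**

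| Feature | Verum | Sham | Shared? |
|---|---|---|---|
| Skin penetrated | yes (2 cm) | no | no |
| Needle at the acupoint | yes | no (1.5 cm lateral) | no |
| Sponge pad, manipulation procedure, course | yes | yes | yes |

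Penetration is in the not-shared rows, so it cannot produce activation common to both conditions.

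**Step 2: what the task contrast measures, by 2.6.2.** Within each run, blocks of twisting alternate with blocks in which the needle is retained. The needle is in position in both block types, and 2.5.1 places insertion and Deqi before the task blocks. The within-run contrast is therefore manipulation against retention. The act of insertion is not isolated even under verum. Static needle contact is likewise constant across blocks and drops out.

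**Step 3: what shared task activation can reflect.** What remains common to both conditions across the blocks is the response to manipulation relative to retention, with the attention and expectation that go with it.

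**Step 4: where a penetration response goes.** Verum and sham differ in both penetration and location, so

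verum − sham = effect of penetration + effect of location (including any interaction).

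Each participant has only two conditions: penetrating at the acupoint, and non-penetrating at the non-acupoint. Penetration and location change together, so the two terms cannot be separated. In the task contrast the penetration term is the difference between twisting a needle in tissue and twisting one on the skin. In the pre/post resting-state comparison it also includes having been needled through the skin.

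**Step 5: compare with 3.5.** That section labels the whole difference specific. By step 4 it includes a component that 3.1.1 labels non-specific. The two labels cannot both hold under 2.5.2.

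**The case against.** The strongest reply is that 3.1.1 is anticipated interpretation, hedged, in a paper with no data. It fixes no endpoint, contrast or threshold, and correcting it changes no computed quantity. That is right and limits the weight of the point. It does not remove it, because the sentence states what shared activation will be taken to mean, and 3.5 relies on the same division.

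Three stronger readings may tempt a reader, and the document does not support them.

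- *That a planned map of verum–sham common activation will be mislabelled.* No such map is planned. The common-effects analysis in 2.7.4 concerns acupoint stimulation, and the abstract speaks of patterns common across acupoints. Section 2.7.3 names one-sample tests, a repeated-measures ANOVA and paired tests, but no verum–sham conjunction. The issue is how shared activation is interpreted.
- *That 2.3 creates a second, equal contradiction by putting sham on the acupoint.* The phrase follows a statement of the number of participants per point and reads as shorthand for the acupoint group. The abstract, 2.1, 2.5.2 and 2.7.3 all place the sham at a non-acupoint. This is a matter of wording.
- *That 3.1.1 could be repaired by naming needle contact as the shared source.* Contact is constant across both block types (step 2), so the task contrast does not isolate it either.

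It may also be said that penetration is part of real acupuncture, so that a difference including it is fairly called an effect of acupuncture. That is a defensible estimand, but it is not an effect of the acupoint, and it does not fit 3.1.1's classing of penetration as non-specific.

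**Conclusion.** The point holds as an inconsistency between the stated interpretation and the described control. Under 2.5.2, penetration cannot be a source of activation shared by verum and sham. Any penetration response lies in the verum–sham difference, inseparable from location, and 3.5 reads that difference as specific.

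The size is qualitative. Conduct, analyses and computed results are unaffected. Because 2.5.2 describes one form of sham for every point, the limit on interpretation applies at all seven acupoints. The conclusion assumes that 2.5.2 describes the sham as it will be delivered; if 3.1.1 reflects the intended control instead, 2.5.2 is the section in error. The document does not settle which, and this review does not choose. The correction is worth making because it costs little and bears on what the trial may conclude.

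**What to change.** Reconcile 3.1.1 with 2.5.2 so that one description of the sham stands. If 2.5.2 stands:

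1. In 3.1.1, attribute shared task activation to what both conditions share across the task blocks: needle manipulation versus retention, with the accompanying attention and expectation. State that shared activation carries no information on penetration.
2. In 3.1.1 and 3.5, state that verum–sham differences combine penetration and location, and so cannot be read as effects of the acupoint alone.
3. As a minor wording point, align the phrase on the shared acupoint in 2.3 with the paired non-acupoint in 2.1 and 2.5.2.

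The cost is a few sentences in three sections. The claim about penetration as a non-specific component is dropped, and the claim about acupoint-specific effects becomes narrower. Conduct and computed results do not change.

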#### Differential brain effects

3.1.2

Verum acupuncture is hypothesized to produce more robust and widespread brain modulation than sham acupuncture, engaging distinct neural mechanisms. Specifically, it activates subcortical centers (e.g., hypothalamus, brainstem) and limbic regions (e.g., amygdala, hippocampus), implicating its role in autonomic, affective, and homeostatic regulation. In parallel, it more strongly suppresses the core default mode network (DMN), including the posterior cingulate and medial prefrontal cortices. This pronounced DMN deactivation may reflect an enhanced redirection of attention toward bodily stimuli, aligning with the concept of “regulating the spirit” and distinguishing the holistic action of verum acupuncture.

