### Blinding assessment and placebo effects

3.5

The blinding assessment may show that a portion of participants cannot accurately distinguish between verum and sham acupuncture, with a potentially high proportion selecting “uncertain.”

If the subjective guesses between groups do not differ significantly, then the differences in brain responses are more likely attributable to the biological effects of acupuncture itself rather than participant expectation. This would enhance the credibility of the findings. Even if placebo effects are present, this study is well-designed to dissociate them (common effects) from the specific effects (differential effects) using neuroimaging.

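### A stronger DMN deactivation under verum is read as more attention and yet as specific, although the article counts attention among the non-specific components

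*Protocol article*

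**What the plan says.** Three statements in the protocol article bear on this.

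- Section 3.1.1 (Common brain effects) describes a network that both verum and sham may activate, "reflecting the non-specific effects of acupuncture". It explains that "this brain activity largely stems from shared components such as attention, sensation, and expectation elicited by the skin penetration itself". It adds a link to placebo by describing the same activity as "overlapping with the neural substrates of placebo effects".
- Section 3.1.2 (Differential brain effects) hypothesizes that verum activates subcortical and limbic regions and, in parallel, that "it more strongly suppresses the core default mode network (DMN), including the posterior cingulate and medial prefrontal cortices". It continues: "This pronounced DMN deactivation may reflect an enhanced redirection of attention toward bodily stimuli". The same sentence describes this as "distinguishing the holistic action of verum acupuncture".
- Section 3.5 (Blinding assessment and placebo effects) says that, even if placebo effects are present, the study is well designed to "dissociate them (common effects) from the specific effects (differential effects) using neuroimaging".

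The two conditions are described in section 2.5. Verum is inserted to 2 cm and manipulated after Deqi. Sham is a blunt needle resting on the skin, without penetration and with slight pressure. Section 2.7.3 compares the two with paired t-tests.

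**The concern.** Attention appears on both sides of the line between non-specific and specific. When both sessions engage it equally, it belongs to the placebo-like response. When verum engages more of it, the excess becomes a mark of what verum does distinctively. More of a component that the article itself calls non-specific does not become specific by being larger.

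The first objective in the Introduction is to isolate the specific central effects of an acupoint from non-specific responses. A needle that is felt more strongly may draw more attention to the body and so deactivate the DMN more, with no acupoint-specific mechanism at work. Under the reading in sections 3.1.2 and 3.5, that result would support a specific effect. The Discussion adds weight, because it names the extent of DMN suppression as a candidate biomarker for treatment response.

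**Working it through.** **Setting the passages side by side.** The article states no figure on this point, so there is none to reproduce. The check is mainly one of reasoning.

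1. Write the DMN response in a session as a non-specific part N (attention, sensation, expectation) plus a specific part S. For sham, S is zero by design.
2. The paired contrast is then (N_verum + S) − N_sham = (N_verum − N_sham) + S.
3. The contrast equals S only if N_verum = N_sham. Subtracting sham removes the shared amount of N and leaves any excess.
4. The article gives reason to doubt equality. Section 3.1.1 ties the shared components to skin penetration, but the sham in section 2.5.2 does not penetrate. Section 3.1.2 itself expects attention to be greater under verum.
5. Section 3.5 nevertheless assigns the common part to placebo and the differential part to specific effects. That assignment requires the equality in step 3.

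**Do other parts of the article close the gap?**

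- The guess question (2.6.3, 3.5) addresses belief about which treatment was given. It does not measure attention or felt intensity.
- The last limitation in the Discussion concedes that sham may not eliminate placebo effects. It does not mention unequal attention or sensation.
- Section 3.3 expects C-MMASS intensity to correlate with insula and ACC activation. It names no DMN analysis and does not use felt intensity to qualify the verum-sham contrast.

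**Illustration of size.** Inputs: n = 30 per acupoint (section 2.3); voxel-wise p < 0.005 (section 2.7.3), taken as two-sided; S = 0. The paired standardized difference d is assumed, because the document gives none.

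The probability of flagging the difference is P(|T| > t_crit), where T is noncentral t with 29 degrees of freedom and noncentrality d × √30, and t_crit = 3.038.

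| Assumed d | d × √30 | Probability flagged |
|---|---|---|
| 0.15 | 0.82 | 0.02 |
| 0.225 | 1.23 | 0.05 |
| 0.3 | 1.64 | 0.10 |
| 0.45 | 2.46 | 0.31 |
| 0.6 | 3.29 | 0.60 |

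These figures ignore the cluster-level correction in section 2.7.3 and apply to a single voxel.

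**The case against.** The strongest reply is that sections 3.1 to 3.5 set out expected results, mostly in hedged language, and that section 2.7.3 only identifies differential patterns without labelling them specific. That stands. A reader might infer that the plan contains a rule by which any verum-sham difference is scored as specific. It does not, and just before the statement at issue section 3.5 makes attribution to acupuncture conditional on similar guesses in the two conditions. What survives is that the statement itself, on what the design can dissociate, carries no hedge.

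A second reply is that 3.1.1 concerns activity common to both conditions, largely in other regions, while 3.1.2 concerns a difference in degree. This also stands in part. A reader might infer a flat contradiction, but a component can be shared at one level and still differ in amount. The fault is one of inconsistent classification.

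Two further strong readings fail. DMN suppression is not presented as the leading marker of verum; it is listed alongside subcortical and limbic activation, which this point does not touch. Nor do the documents support a high false-claim rate. A single test at two-sided 5% would give 0.355, 0.664 and 0.888 for d = 0.3, 0.45 and 0.6, but section 2.7.3 sets a stricter voxel threshold plus a cluster step, and every d is assumed. The calculation shows that the contrast can detect an attentional difference, not that one exists.

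Finally, C-MMASS adjustment is an imperfect remedy. It rates sensation rather than attention, and Deqi is sought as part of verum, so it may lie on the causal path. This is a good reason not to let the adjusted result decide.

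**Conclusion.** The point holds as an inconsistency of interpretation. Section 3.1.1 treats attention and sensation as non-specific, section 3.1.2 treats more attention under verum as distinguishing, and section 3.5 equates differential with specific. With a light-touch, non-penetrating sham, the contrast cannot separate a larger non-specific response from a specific one.

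The conclusion rests on the article's own wording and on the sham's not being matched for sensation; it needs no number. The 10%, 31% and 60% figures are illustrative only. They assume a purely attentional difference of the stated size, and at half the smallest of those effects (d = 0.15) the probability is about 2%. The change is worth making because it limits what a positive DMN finding can be said to show.

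**What to change.** In sections 3.1.2 and 3.5, replace the claim that differential effects are the specific effects. State instead that a verum-sham DMN difference may reflect greater attention or felt intensity and is not by itself evidence of a specific effect.

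As a sensitivity analysis, report the verum-sham DMN contrast twice: unadjusted, and with the within-person verum-sham difference in C-MMASS intensity in the model. Do not make the adjusted result the criterion for calling an effect specific. State three limits beside it:

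- C-MMASS measures sensation, not attention.
- Adjustment may remove an effect that acts through Deqi.
- Section 2.6.4 places the ratings after both trials, so first-session ratings may rely on recall about a week later.

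The cost is a few sentences and one additional model using a scale already planned. No new data collection is needed.
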